#### Method of Dealing With Missing Data

Descriptive analyses will use all available data. Inferential analyses (eg, linear regression and growth curve modeling) will use multiple imputation (with chained regression equations) as the primary method of dealing with missing data. The number of imputed data sets will depend on the fraction of missing data, but the stability of results will be assessed over a range of imputation numbers.

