### Overview of the mHealth Routine Outcome Monitoring and Feedback App (Smart Track)

The Smart Track app was designed for participants attending SMART Recovery groups. ROM items are intended for weekly completion. However, it is up to the individual to decide whether, when, and how they engage with Smart Track. Given the low-risk, low-burden nature of this study, there are no contingencies for discontinuing access to the Smart Track app. Owing to app store regulations, Smart Track will not be restricted to study participants. It will be freely available for download through Android and iPhone Operating System stores (only data from those who provide consent will be included in the study).

Publications detailing the methods and findings from the qualitative work [33] and app development process (including theoretical foundations) will be reported separately. To provide context, a brief summary is presented here. The Smart Track app was developed during the first phase of this study using participatory design workshops and an iterative development process informed by the (1) consideration of existing ROM tools, (2) qualitative feedback [33] and usability testing sessions with SMART Recovery participants and facilitators, (3) clinical and research expertise from the members of the expert advisory and steering committees, and (4) technological and creative expertise of the development team employed to work on this study (GHO, Sydney) [34].

The functionality of Smart Track was initially tested with 3 members of the research team. Several bugs were identified and fixed before the amended beta version was released to a convenience sample (n=40) for further testing. This convenience sample of beta testers included members of the expert advisory committee, steering committee, SMART Recovery board members, and SMART Recovery facilitators. Further refinements were made in line with the feedback received (bug fixes, minor amendments to functionality, and content).

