##### Preliminary Psychometrics of Smart Track ROM Items

Preliminary psychometrics for Smart Track items will be explored via sensitivity to change, internal consistency, test-retest reliability, convergent validity, and exploratory factor analysis. Internal consistency of Smart Track ROM items will be evaluated using Cronbach alpha coefficient. Pearson correlation analysis will be used to examine the test-retest reliability of ROM scores for the first and second completion of each item set. Convergent validity will be examined using Pearson correlation analysis to explore the associations of initial ROM scores with the standardized measures (COMS and SURE) administered at baseline. Sensitivity to change will be examined via effect sizes, reliable change index (RCI), and growth curve modeling. As appropriate, internal consistency, test-retest reliability, concurrent validity, and RCI will be further examined as a function of age group, gender, and primary behavior of concern.

Effect sizes will be estimated for participants’ average ROM change scores between the first and last sessions. To explore the minimum reliable amount of change in scores (while accounting for measurement error [78]), we will calculate RCI between participants’ first and last ROM scores. The Jacobson and Traux criteria [78] will be applied to describe the proportion of participants who improved, did not change, or deteriorated. RCIs will also be calculated for the standardized measures administered at baseline and follow-up to allow comparisons with the ROM items. Growth curve modeling will be used to estimate the average rates of change in ROM scores across the 2-month period of ROM usage.

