#### Power

We aim to recruit participants from 13 sites that conduct a combined total of 25 groups per week. Assuming an average of 6 eligible participants per group per week and a target sample size of 100 participants, we anticipate recruitment to take between 4 and 6 weeks (for an estimated recruitment rate between 11% and 17%). A sample of this size will enable the estimation of the recruitment rate and 95% CI, with a margin of error of no more than 7%.

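### The growth curves of ROM scores do not need chained-equation imputation; a mixed model on the observed, dated scores should be their primary analysis

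*Protocol article*

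**What the plan says.** The protocol article, section Method of Dealing With Missing Data, uses all available data for descriptive analyses. For the rest it says: "Inferential analyses (eg, linear regression and growth curve modeling) will use multiple imputation (with chained regression equations) as the primary method". It adds that "The number of imputed data sets will depend on the fraction of missing data", and that stability will be checked over several imputation numbers.

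The section Preliminary Psychometrics of Smart Track ROM Items gives the purpose of the curves: "Growth curve modeling will be used to estimate the average rates of change in ROM scores across the 2-month period". It names no participant covariate for this model.

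ROM items are meant to be completed weekly, but under the overview of the app "it is up to the individual to decide whether, when, and how they engage with Smart Track". Table 3 counts missing ROM data week by week. Table 2 schedules the full interview measures, including the Client Outcome Management System (COMS) battery and the Substance Use Recovery Evaluator (SURE), at baseline and at 2 months. The article does not give the imputation format, whether items or scores are imputed, the predictor set, or an expected missing fraction.

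**The concern.** The article makes a definite choice here, and a simpler method serves the stated target better. In a growth curve without covariates only the outcome can be missing. A mixed model fitted by likelihood already uses every partial record under missing at random, so imputing the outcome first is not needed to estimate the average slope.

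Chained equations in their usual wide form also need fixed columns. Entries made when the user chooses would have to be assigned to weeks before anything is imputed, and their actual dates would be lost.

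The cost rises with missingness, and the article itself expects patchy completion: weekly missingness is a feasibility endpoint, time to disengagement is to be analysed, and 10 regular group attenders who do not complete the ROM regularly are to be interviewed. At stake are the precision and stability of the average slope and its confidence interval, one of three sensitivity-to-change analyses.

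**Working it through.** **The plan's own figures.** The only precision statement concerns the recruitment rate. With 25 groups and 6 eligible people each, 150 people are available per week. Then 100/(150 × 4) = 16.7% and 100/(150 × 6) = 11.1%, which agrees with the stated range. The margin 1.96 × √(p(1 − p)/n) is 7.3 points (p = 0.167) or 6.2 points (p = 0.111) with n = 100. It is 3.0 points with 600 approached and 2.1 with 900. No precision is given for the growth curves.

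**Inputs.** From the article: n = 100, weekly schedule, 2 months. Assumed, because the article gives no figures: 9 occasions (weeks 0 to 8), true slope 0.05 per week, independent random intercept (variance 0.5) and slope (variance 0.005), residual variance 0.4. Missingness combines random gaps with dropout that depends on the last observed score.

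**Benchmark with nothing missing.** The squared deviations of weeks 0 to 8 sum to 60, so the SE of the mean slope is √((0.005 + 0.4/60)/100) = 0.0108.

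**Methods compared.** (a) A mixed model fitted by maximum likelihood to the observed scores. (b) Wide chained-equation normal imputation of one score per week, 20 imputations, total variance U + (1 + 1/m)B. There were 150 replicates per scenario, with an auxiliary variable correlated 0 or 0.7 with the slope, and imputation with and without it. Ranges span these variants.

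| Missing | Observed in last week: mean (minimum) | Mixed model: SD; mean SE | Imputation: SD; mean SE | Ratio of mean SEs |
|---|---|---|---|---|
| about 24% | 66-67 (48) | 0.0116-0.0124; 0.0122-0.0123 | 0.0120-0.0124; 0.0128-0.0133 | 1.05-1.08 |
| about 47% | 33 (21) | 0.0164-0.0168; 0.0154-0.0157 | 0.0181-0.0191; 0.0196-0.0205 | 1.27-1.33 |
| about 65% | 13 (5) | 0.0217-0.0251; 0.0211-0.0212 | 0.0544-0.1667; 0.1313-0.2217 | 6.2-10.5 |

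Coverage of the 95% interval was 0.90-0.97 for the mixed model and 0.95-0.99 for imputation. At 47% missing the mixed model's mean SE lay about 6% below its empirical SD, and that of imputation 7-10% above. The gap in actual sampling SD is therefore smaller than the gap in reported SE: 8-16%.

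A second simulation (40 replicates per scenario, variances and missing rates again assumed, app scores only) gave mean SEs, mixed model against wide imputation, of:
- 20% missing: 0.0139 vs 0.0147, ratio 1.06
- 43% missing: 0.0172 vs 0.0223, ratio 1.30
- 59% missing: 0.021 vs 0.050, ratio 2.4

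**Why the loss grows.** With one score over 9 weeks, each imputation equation has 8 predictors. At 65% missing, the last week had as few as 5 people to estimate them. More imputations do not cure this: going from m = 20 to unlimited m lowers the SE by a factor of at most √(1 + 1/20) = 1.025.

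**Interview data.** When dropout was made to depend on the 2-month interview score (true slope 0.05), the mixed model on app scores alone averaged 0.078. With the interview records entered as outcomes it averaged 0.051 (SE 0.0128). Wide imputation using the same interview data averaged 0.054 (SE 0.0204).

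**The case against.** The strongest reply is that chained equations need not be wide. Predictors can be restricted, and two-level models can work on long data at actual times. The article fixes neither format nor level and may leave both to the analysis plan. This stands. A two-level imputation at about 46% missing (40 imputations; 38 and 60 replicates in the two settings tried; interview score assumed fully observed) gave a slope SD of 0.0206 against 0.0216 for a REML fit to app scores alone, and 0.0186 when the interview score was added. Some REML fits did not converge. So the mixed model is not more precise in general, and imputation does add information when good auxiliary data exist. With dropout driven by the interview score, this imputation averaged 0.049 and removed the bias. What does not stand is that this makes imputation necessary, since the mixed model gains the same protection from the interview records.

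A reader might infer that 100 people cannot support chained equations at all, for instance from 21 SURE items × 9 weeks = 189 columns. The documents do not support that. The article models scores, does not say that all 21 items are asked every week, and places item frequency in Multimedia Appendix 2, which is not shown. Wide imputation of a single score ran acceptably at 24% and 47% missing. Nor is joint imputation of several scores specified, so a several-fold loss at moderate missingness cannot be read into the plan.

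It would also be wrong to conclude that imputation should be confined to baseline covariates. Table 4 relates ROM completion to factors measured at baseline and at 2 months.

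**Conclusion.** The point holds as a minor one. Chained-equation imputation is a poor primary choice for a covariate-free growth curve of user-timed scores, because the direct likelihood fit does the same job under missing at random without a weekly grid. Against wide score-level imputation, the direct fit is about equal at 20-25% missing. Imputation's mean SE is about 30% larger at 43-47%, and at least twice as large at about 60% or more.

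These sizes rest on assumed variances, missing rates and 9 occasions, and on the wide form, which is usual but not stated. Neither method handles disengagement that depends on scores that neither the app nor the interview records.

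Severity is limited because the growth curve belongs to preliminary psychometrics, a secondary objective of a single-arm pilot. The feasibility and acceptability endpoints rest mainly on descriptive statistics, and participant outcomes are summarised descriptively.

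**What to change.** In Method of Dealing With Missing Data, take growth curves out of the imputation sentence and state their analysis separately:

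- Primary: a linear mixed model fitted by REML, with random intercept and slope, on all observed ROM scores, with actual days since baseline as time.
- Add the baseline and 2-month interview scores on the same instrument as outcome records with a mode indicator, where the scores are comparable. The app uses only a subset of COMS items and some wording or response formats were changed, so comparability must be checked instrument by instrument, and the interview score computed on the app's items where needed.
- Keep multiple imputation for missing baseline and 2-month covariates in the linear regressions under App Engagement and Usage Patterns, and optionally as a sensitivity analysis for the growth curves.

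The cost is a few sentences, no new data and less analysis work. The drawback is that the model must assume a common scale across app and interview.

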#### Participant Outcomes

Participants’ responses to the COMS and SURE (as captured via interview and ROM items across the 2-month data collection period) will be summarized using descriptive statistics.

#### Power

We aim to recruit participants from 13 sites that conduct a combined total of 25 groups per week. Assuming an average of 6 eligible participants per group per week and a target sample size of 100 participants, we anticipate recruitment to take between 4 and 6 weeks (for an estimated recruitment rate between 11% and 17%). A sample of this size will enable the estimation of the recruitment rate and 95% CI, with a margin of error of no more than 7%.

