### Study Outcomes

Primary and secondary endpoints are presented in Tables 3 and 4, respectively.

**Table 3 table3:** Primary endpoints.

Primary objective	Primary endpoint
To explore the feasibility of using Smart Track as part of SMART^a^ Recovery groups for the purposes of ROM^b^ and tailored feedback	Proportion of eligible participants who consent to the study Proportion of missing data for each of the ROM items/instruments at each week of administration, across the 2-month period of Smart Track usage Costs associated with developing Smart Track and maintaining the app until the completion of data collection Participant engagement with Smart Track, as indexed by data analytics captured daily across the data collection period
To explore the acceptability of using Smart Track as part of SMART Recovery groups for the purposes of ROM and tailored feedback	Detailed qualitative feedback from SMART Recovery group members and facilitators to explore their experience of and satisfaction with Smart Track (2-month follow-up) Quality ratings as assessed by participant and facilitator ratings of the user version of the Mobile App Rating Scale (2-week follow-up) and Mobile App Rating Scale (2-month follow-up), respectively Digital therapeutic alliance ratings as assessed by participant ratings of the Digital Working Alliance Inventory (2-week and 2-month follow-up)

^a^SMART: Self-Management and Recovery Training.

^b^ROM: routine outcome monitoring.

**Table 4 table4:** Secondary endpoints.

Secondary objective	Secondary endpoints
To explore how participants engage with the app and describe usage patterns	Demographic, clinical, and treatment factors (as measured by Client Service Receipt Inventory, COMS^a^, and SURE^b^ at baseline and 2-month follow-up) associated with (in)completion of Smart Track ROM^c^ items Data analytics captured daily across the data collection period
To provide preliminary evidence for the psychometric properties of the ROM items administered by Smart Track	Internal reliability and convergent and divergent validity of COMS and SURE items administered by Smart Track (relative to the complete versions administered at baseline and 2-month follow-up)

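### The recruitment-rate margin of error is tied to the 100 recruits, who are the numerator; on the plan's own count of eligible people it is about 2 to 3 points, not 7

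*Protocol article*

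**What the plan says.** The Power section of the protocol article plans to recruit from "13 sites that conduct a combined total of 25 groups per week". It continues "Assuming an average of 6 eligible participants per group per week", sets "a target sample size of 100 participants", and concludes that "we anticipate recruitment to take between 4 and 6 weeks", with the rate given as "for an estimated recruitment rate between 11% and 17" per cent. The next sentence opens "A sample of this size will enable the estimation of the recruitment rate"; its full claim is that this sample will "enable the estimation of the recruitment rate and 95% CI, with a margin of error of no more than 7" per cent. The only sample size named in the paragraph is 100.

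Study Outcomes, Table 3, lists the rate as the first feasibility endpoint and defines it as the share of eligible people who consent.

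Two other sections bear on the denominator. Eligibility covers people currently taking part in one or more groups. Enrollment has facilitators follow up expression-of-interest forms with participants over as many as three meetings.

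**The concern.** A margin of error for a proportion depends on its denominator. Table 3 makes that the number of eligible people, and the 11% to 17% is itself worked out on that basis. The precision sentence then attaches the margin to the 100 who consent. One paragraph thus seems to use one denominator for the rate and another for its precision.

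This sentence is the only quantitative justification for the sample size in the article. The primary objectives are analysed mainly with descriptive statistics, so precision is the whole rationale. A reader should be able to tell what the study will deliver for the recruitment rate, and at present cannot.

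**Working it through.** **Inputs, all from the Power section:** 25 groups per week, 6 eligible people per group per week, 4 to 6 weeks of recruitment, 100 recruits, 95% confidence. The definition of the rate comes from Table 3.

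**Step 1. Reproduce the rate.** 25 × 6 = 150 eligible per week. Over 4 weeks that is 600, and over 6 weeks 900. Then 100/600 = 16.7% and 100/900 = 11.1%, which matches the stated 11% to 17%. The plan's own denominator is therefore 600 to 900.

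**Step 2. Try to reproduce the 7%.** Half-width = 1.96 × √(p(1 − p)/n).

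| n | p | Half-width (points) |
|---|---|---|
| 100 | 11% | 6.13 |
| 100 | 15% | 7.00 |
| 100 | 16.7% | 7.30 |
| 100 | 17% | 7.36 |
| 600 | 100/600 = 16.7% | 2.98 |
| 750 | 100/750 = 13.3% | 2.43 |
| 900 | 100/900 = 11.1% | 2.05 |

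Only n = 100 comes near 7. On that basis the bound holds up to 15% and is slightly exceeded at the stated upper rate. Other intervals at 17% and n = 100 do not bring it down to 7: Wilson gives 7.33, Clopper-Pearson 7.80 and the continuity-corrected interval 7.86. A 7-point margin at 17% would need 1.96² × 0.17 × 0.83 / 0.07² = 110.6, so 111 people.

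**Step 3. Size of the discrepancy.** 7/2.98 = 2.3 and 7/2.05 = 3.4. The exact (Clopper-Pearson) intervals agree with the simple ones: 13.8% to 19.9% for 100/600, and 9.1% to 13.3% for 100/900.

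**Step 4. Unique people.** The 600 to 900 is reached only if each week brings 150 new eligible people. With fewer unique people, N, and 100 consenters, both the rate and the margin move:

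- N = 300: rate 33.3%, margin 1.96 × √(0.333 × 0.667/300) = 5.3 points.
- N = 196: rate 51.0%, margin 7.0 points.
- N = 150 (the same people every week): rate 66.7%, margin 1.96 × √(0.667 × 0.333/150) = 7.5 points.

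With 100 consenters, N = 150 gives the largest margin of any N.

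**Step 5. Clustering (the ICCs are assumptions; the article gives none).** Design effect = 1 + (m − 1) × ICC, with m = 600/13 = 46.2 per site. At ICC 0.05 it is 3.26, and 2.98 × √3.26 = 5.4 points. At ICC 0.10 it is 5.52, and 2.98 × √5.52 = 7.0 points. The agreement of the latter with the stated 7% looks like coincidence, since the article mentions neither an ICC nor a design effect.

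**The case against.** The strongest reply is that the sentence gives an upper limit, and on the correct denominator that limit is met: 2 to 3 points is no more than 7. It is still met, at 7.0, with an assumed site ICC of 0.10 and 600 people. Without clustering it is met whenever at least 196 unique people are approached. For recruitment, then, the claim is loose and does not overpromise. This stands, and it limits the severity. It does not rescue the sentence, because a figure two to three times too wide, attached to the wrong count, does not describe the precision expected.

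It can also be said that the use of n = 100 is only inferred. That is true. The inference rests on the wording and on the numerical match in step 2.

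A reader might go further in three directions that the article does not support.

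- **That the bound is plainly false at 17%.** The excess is 7.3 to 7.4 against a figure given in whole per cent, and it arises only on the inferred n = 100.
- **That precision for completeness of routine outcome monitoring (ROM) is misstated.** Table 3 does list "Proportion of missing data for each of the ROM items/instruments at each week of administration", and with 100 participants the margin there could reach 1.96 × √(0.5 × 0.5/100) = 9.8 points. The Power section, however, makes no precision claim for that endpoint.
- **That ignoring clustering is an error in itself.** Any ICC is an assumption, and a cluster-adjusted interval is commonly left to the analysis plan.

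**Conclusion.** The point holds as an error of denominator in the stated precision. The margin is tied to the 100 recruits, while the endpoint and the plan's own rate use the eligible people. With 600 to 900 unique and independent people, the 95% margin is 3.0 to 2.05 points, so the stated 7 is about 2.3 to 3.4 times too wide. If attendances repeat, the rate rises above the stated range and the margin widens, to at most 7.5 points at 150 unique people before any clustering.

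It would be wrong to conclude that 100 participants are too few for this endpoint. On the plan's own count the error is conservative, and the Power section attaches no test or decision threshold to the margin. Severity is minor to moderate.

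**What to change.** Rewrite the precision sentence so that it:

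- defines the denominator as unique eligible people approached, each counted once however many meetings they attend;
- gives the expected number of such people and the resulting expected rate;
- states the 95% margin on that number: about ±2 to 3 points if 600 to 900 are unique and independent, and up to ±7.5 if only 150 are;
- notes that clustering within the 13 sites would widen it, for example to about ±5.4 points at 600 people under an assumed ICC of 0.05.

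Optionally, add a separate statement for ROM completeness with 100 participants (up to ±9.8 points before clustering). This would be an addition, not a correction.

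The cost is one paragraph of text and a count of unique people approached at the sites. No additional participants are needed, and no endpoint changes.
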